### Inclusion criteria

Both genders, age of 40 years or over.Total blood cholesterol levels ≥ 200 and ≤ 250 mg/dL.No history of clinically relevant cardiovascular events.

### Exclusion criteria

A therapy with statins or food supplements with lipid-reducing effects.A therapy with anticoagulants, hypothyroidism or hyperthyroidism.Diabetes.Intestinal malabsorption.Acute illnessesNeoplastic disease or life expectancy less than 1 year.Statin non-related liver disease.Severe chronic renal failure.Allergy/intolerance to one or more components of dietary supplement or placebo.Participated in another clinical trial of intervention in the previous 3 months.Presence of cognitive disorders and other impediments that do not guarantee the correct adherence to the study treatments.There are current or presumed pregnancy and pregnancy planning.Incapacity, impossibility, or unavailability to sign the written consent.

### Randomization

After checking the inclusion and exclusion criteria, subjects’ randomization into the two parallel treatment arms will be carried out by the distribution of a blinded treatment kit containing test or placebo capsules. The capsules will be randomly assigned into the test and placebo groups at a 1:1 ratio according to the random number generated by SPSS v25.0 software package (SPSS Inc., Chicago, IL, USA).

### Blinding

The randomization will be performed using a code list created by the statisticians of the INRCA Biostatistical Center. The trial staff will not know the arm of allocation (double-blind study). The INRCA Hospital Pharmacy will prepare treatment kits assigning them the identification codes following the randomization lists. Only if necessary, for the safety of patients, the single kit code will be open by the investigators during the study period.

### Interventions

Patients will be randomized in two treatment groups:
The first group will be treated with two capsules of a new dietary supplement on a day.The second group will be treated with two capsules on a day with placebo taken in the same way and timing of administration provided for the supplement.

#### Dietary supplement capsules

The new dietary supplement consists of flavonoids extracted from bergamot, olive polyphenols, plant sterols, and vitamin K2. This innovative combination of the above-described components, named BruMeChol™, will be provided by MIVELL s.r.l. (Jesi, AN, Italy). The BruMeChol™ dietary supplement has already received authorization for marketing from the Italian Ministry of Health. The constituents of the BruMeChol™ capsules are summarized in Table 1.

**Table 1 Tab1:** Constituents of the dietary supplement BruMeChol™

*Active substances*	*Amount in capsule*
**Phytosterols**	**400 mg**
**Bergamot fruit**	**100 mg**
Total flavonoid	98 mg
Melitidin and Brutieridin	14.7 mg
**Olive fruit**	**20 mg**
Total polyphenols	19.6 mg
Hydroxytyrosol and derivatives	6 mg
**Vitamin K2**	**52 mcg (49.5% DRVs**^a^**)**

^a^Dietary reference values (DRVs) on a day (Reg. UE 1169/2011)

#### Placebo

The placebo capsule will contain 2% of magnesium stearate, 2% of silicon dioxide, and 96% of calcium phosphate. The placebo will be manufactured to have a similar appearance, shape, weight, taste, and color as BruMeChol™ capsule.

#### Treatments

The subjects will receive either two capsules of BruMeChol™ or placebo daily, one capsule took 15 min before lunch and one capsule 15 min before dinner.

### Study period

The study will last 12 weeks. The visits and the evaluations will be done as follows: screening, baseline-randomization (visit 1), 6 weeks from baseline (1st follow-up, visit 2), and 12 weeks from baseline (2nd follow-up, visit 3). The study schedule at each visit is presented in Table 2.

**Table 2 Tab2:** Study schedule at each visit in the clinical trial

	Study schedule			
	Screening	Baseline (visit 1)	6th week (visit 2)	12th week (visit 3)
Informed consent form	X			
Recording demographic data	X			
Medical history taking		X		X
Physical examination ^a^	X	X	X	X
Glycemia	X	X	X	X
Renal function^b^	X	X	X	X
Liver function^c^	X	X	X	X
Thyrotropin-TSH	X			
Lipid profile^d^	X	X	X	X
Fool blood exam-FBE^e^		X	X	X
Leukocytes formula^f^		X	X	X
Electrolytes^g^		X	X	X
Cardiac/muscular markers^h^		X	X	X
C-reactive protein		X	X	X
Lipoprotein (a)		X	X	X
Interleukins^i^		X	X	X
Inflammatory-miRs^j^		X	X	X
ECG^k^		X		X

^a^Weight, height, waist circumference, and hip circumference

^b^Creatinine; estimated glomerular filtration rate by CKD-EPI equation

^c^Aspartate aminotransferase glutamic oxaloacetic transaminase (AST/GOT), alanine aminotransferase/ glutamic pyruvic transaminase (ALT/GPT)

^d^Total cholesterol_,_ triglyceride, low-density cholesterol (LDL), and high-density cholesterol (HDL)

^e^White blood cells (WBCs), red blood cells (RBCs), hemoglobin, hematocrit, mean cell volume (MCV), mean corpuscular hemoglobin (MCH), mean corpuscular hemoglobin concentration (MCHC), red cell distribution width (RDW), platelets

^f^Neutrophils, eosinophils, basophils, lymphocytes, monocytes

^g^Sodium, potassium, chlorine, calcium, phosphorus, magnesium

^h^Cardiac Markers Creatine Kinase (CK)/ myoglobin

^i^IL6, IL32, IL37, IL38

^j^miR-21 and miR-146a

^k^Electrocardiography

### Outcomes

#### Primary outcome

The primary outcome is the change in serum total cholesterol levels after 12 weeks of post-intervention commencement between experimental arm and placebo comparator arm.

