##### Biochemical profile

Screening visit will include following measurements: total cholesterol, fasting glucose, liver profile (AST/GOT, ALT/GPT), kidney profile (creatinine, CKD-EPI e-GFR) and thyrotropin (TSH). Serum lipid profile: total, LDL, HDL cholesterol and triglycerides, liver profile (AST/GOT, ALT/GPT), kidney profile (creatinine, CKD-EPI e-GFR), fasting glucose, fool blood exam (FBE), leukocyte formula, electrolytes, cardiac/muscular markers (CK/myoglobin), CRP, and Lp(a) will be measured at baseline, 6 weeks, and on completion of the study (12 weeks from randomization). All items that will be measured at every visit are described in Table 2.

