### Statistical analysis

Demographic, clinical characteristics and outcomes data will be summarized with counts and percentages for categorical variables, means (standard deviations) for normally distributed continuous variables, and medians (with interquartile ranges) for other continuous variables. Kolmogorov-Smirnov test will be used to check the normality of the related variables. Repeated measures analysis of variance (ANOVA) will be used to test whether treatment (between-subjects factor) differentially affect the mean values of cholesterol levels (within-subjects factor) over time. The same analysis will be also repeated for the inflammatory biomarkers that will be used as within-subjects’ factors. Mauchly’s test will be used to assess the assumption of sphericity, and Greenhouse-Geisser correction will be adopted for violations of this assumption. A significant level of 0.05 will be used throughout the study. Statistical analyses will be performed with IBM SPSS statistical software ver. 25.0 (IBM Corp., Armonk, NY, USA).

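### Total cholesterol is scheduled twice before treatment but only visit 1 is labelled baseline; averaging or adjusting for both values would gain some precision at little cost

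*Protocol article*

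**What the plan says.** The Primary outcome section of the protocol article reads "The primary outcome is the change in serum total cholesterol levels after 12 weeks of post-intervention commencement", compared between arms. It does not name the value from which the change is taken.

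The Study period section lists the visits as "screening, baseline-randomization (visit 1), 6 weeks from baseline (1st follow-up, visit 2"), followed by "12 weeks from baseline (2nd follow-up, visit 3"). Screening and baseline are therefore separate occasions, and follow-up is counted from visit 1.

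Both occasions include total cholesterol. Under Biochemical profile, "Screening visit will include following measurements: total cholesterol, fasting glucose" and other tests; the serum lipid profile, total cholesterol included, "will be measured at baseline, 6 weeks, and on completion of the study (12 weeks from randomization"). Table 2 ticks the lipid profile at screening and at all three later visits. Its footnote defines the profile as total cholesterol plus "triglyceride, low-density cholesterol (LDL), and high-density cholesterol (HDL").

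Entry requires "Total blood cholesterol levels ≥ 200 and ≤ 250 mg/dL", without saying which sample decides. The Statistical analysis section plans a repeated-measures ANOVA of whether treatment will "differentially affect the mean values of cholesterol levels (within-subjects factor) over time". It lists no time points and no baseline covariate.

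**The concern.** A change from one pre-treatment sample carries the whole within-person error of that sample. Entry is confined to a 50 mg/dL band, which compresses the true differences between subjects, so within-person variation makes up a large share of any single value. In a repeated-measures ANOVA with visit 1 as the first level, that error enters the 12-week treatment contrast in full.

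A second pre-treatment value is already scheduled and assayed. If it serves only for eligibility, the treatment difference is estimated with more noise than necessary. What is at stake is precision and power, not bias.

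**Working it through.** **The plan's own figure.** Sample size section: d = 0.5, power 0.85, type I error 0.05, 59 per arm, 118 in total, 125 with 5% dropout. The normal formula is n per arm = 2(z_α + z_power)²/d².

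- One-sided: 8 × (1.645 + 1.036)² = 57.5, so 58; the exact t calculation gives 59, hence 118.
- Two-sided: 8 × (1.960 + 1.036)² = 71.8, so 72; 73 with t. At 59 per arm, two-sided power is about 0.77.
- Dropout: 118/0.95 = 124.2, so 125.

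The figure reproduces only as a one-sided test; the protocol does not state sidedness, and that is a separate matter. The calculation concerns cholesterol levels at the second follow-up. No baseline enters it, so the choice of baseline does not alter it.

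**Variance of the change, no selection on entry.** Let S, B and Y be the screening, visit 1 and week 12 values, with common variance σ² and common correlation r.

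- Var(Y − B) = 2σ²(1 − r)
- Var(Y − (S + B)/2) = σ² + σ²(1 + r)/2 − 2rσ² = 1.5σ²(1 − r)
- Ratio = 0.75 for any r below 1, a 25% cut.

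If the within-person errors at S and B have correlation c, while the error at Y is independent of both, the ratio is (3 + c)/4. That gives 0.75 at c = 0, 0.875 at c = 0.5 and 0.95 at c = 0.8.

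**Baseline as a covariate, no selection.** Residual variance is σ²(1 − r²) with B alone and σ²[1 − 2r²/(1 + r)] with the mean of two. At r = 0.5 this is 0.750 against 0.667, an 11% cut. At r = 0.8 it is 0.360 against 0.289, a 20% cut.

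**With entry at 200–250 mg/dL on screening (simulation).** Assumed, because the documents give none of these: population mean 210–220, true SD 30–40, within-person SD 11–18 mg/dL.

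| Error correlation, screening to visit 1 | Cut in change-score variance | Cut in residual variance, baseline as covariate |
|---|---|---|
| 0 | 26–28% | 6–13% |
| 0.5 | 13–16% | 4–8% |
| 0.8 | 6–8% | 2–4% |

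Adding drift in each subject's true level before week 12 lowers the gain further. At correlation 0.8 with such drift, the cut in change-score variance reaches about 4%. The gain was positive in every setting examined. Entering both values as covariates gave the same gain as entering their mean.

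**Meaning for power (illustration).** Suppose d = 0.5 were in units of the SD of change; the protocol speaks of levels, so this is an assumption. With 59 per arm and a two-sided 0.05 test, power = Φ(d√(59/2)/√ratio − 1.96), and d√(59/2) = 2.716.

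- Ratio 1: Φ(0.756) = 0.775
- Ratio 0.75: Φ(1.176) = 0.880
- Ratio 0.96: Φ(0.812) = 0.79

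**Bias.** Both values precede treatment. Selection on screening shifts the mean change by the same expected amount in each arm (up to about 3 mg/dL in these simulations), so the between-arm difference is unaffected.

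**The case against.** The strongest reply has five parts.

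- **Visit 1 alone is not stated.** A reader might infer that the protocol fixes visit 1 as the only starting value. It does not: the primary outcome names no starting value, the ANOVA lists no time points, and nothing excludes screening. The inference rests on the visit label. This stands, and the point must be worded accordingly.
- **A single baseline is legitimate.** It is common and unbiased, and its derivation is often left to an analysis plan or full protocol, neither of which is shown. This stands too: nothing is contradicted, and the absence of a definition here is not a defect. What remains is that the reading the article invites can be improved.
- **The larger gain is a best case.** A reader might conclude that averaging is worth about 35% more subjects (1/0.74 = 1.35). That needs independent errors at the two visits, no drift and an unadjusted change score. The interval between screening and visit 1 is not given; if it is short, errors may well be correlated.
- **The model matters.** The direction of the gain holds for change and for covariate adjustment, but the size does not. In the independent-error setting, adjusting for visit 1 alone already cuts variance by 15–24% relative to raw change. The change-score figures describe the 12-week contrast; none was calculated for the overall treatment-by-time test.
- **Recruitment is under way.** Trial status gives a start on 6 March 2018, so redefining baseline is a change during the trial. It is acceptable if made blind to allocation, but it needs documenting.

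**Conclusion.** The point holds as a low-cost improvement. Total cholesterol is scheduled twice before treatment, visit 1 alone carries the baseline label, and the screening value has no stated role in the efficacy analysis. On the natural reading, some precision is given up.

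Under the assumed values, the recoverable share of the variance of the 12-week change runs from about 4–8% (highly correlated errors or drift) to about 26–28% (independent errors, no drift). With covariate adjustment it is about 2–13%. The documents cannot place the trial within these ranges, because they report no SD, no within-person variability and no screening-to-baseline interval.

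They do not support calling this an error, a bias or a flaw in the sample size.

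**What to change.** Before unblinding, define baseline total cholesterol in the Primary outcome and Statistical analysis sections as the mean of the screening and visit 1 values, with visit 1 alone where screening is missing. Alternatively, enter both values as covariates and analyse the post-treatment visits as outcomes. Keep visit 1 alone as a sensitivity analysis.

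If the mean becomes the first level of the repeated-measures ANOVA, it will have a smaller error variance than the other levels. The planned Greenhouse-Geisser correction then becomes more likely to be needed.

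Extend the definition to LDL, HDL and triglycerides only if the full screening profile ticked in Table 2 was drawn; the Biochemical profile section names only total cholesterol among the lipids at screening, and the two should be reconciled. hs-CRP, lipoprotein(a), the interleukins and the miRs are first measured at visit 1 and keep a single baseline.

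Cost: no new visit or assay, but a dated amendment notified to the ethics committee, baseline definitions that differ between outcomes, and a small regression-to-the-mean component in the within-arm mean change, which should be mentioned when within-arm changes are reported.

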#### Secondary outcomes

The secondary outcomes are changes after 6 and 12 weeks post-intervention commencement between experimental arm and placebo comparator arm in the following blood parameters: *hs*-CRP, triglycerides, low-density cholesterol (LDL), high-density cholesterol (HDL), lipoprotein(a), IL-6, IL32, IL37, IL38, miR-21, and miR-146a; and association at baseline between CV risk score evaluated by the SCORE risk charts (www.heartscore.org) and lipid (triglycerides, total, HDL, and LDL cholesterol) as well as inflammatory parameters (*hs*-CRP and IL-6).

### Procedures

#### Subjects recruitment

Advertisements in flyers and trial poster will be available to participants at the IRCCS INRCA hospital, Ancona, Italy.

#### Measurement tools

##### Medical history

Information about the presence or absence of the following data gained by a physician will be taken: hypertension, diabetes, hypercholesterolemia, hypertriglyceridemia, hyperlipidemia, and familiarity for cardiovascular diseases, anemia, chronic renal failure, chronic respiratory failure, dementia, liver disease, digestive system diseases, drug allergies, and surgical interventions.

##### Anthropometric measurements

Body weight will be measured by a calibrated electronic floor scale (FioMed s.r.l Fazzini, Vimodrone, Milano, Italy) to the nearest 0.1 kg. Height will be measured by an upright plastic portable Stadiometer (FioMed s.r.l Fazzini, Vimodrone, Milano, Italy) to the nearest 0.1 cm. Waist circumference will be measured at midway between the iliac crest and the lower costal margin at the end of normal an expiration using a flexible, plastic tape to the nearest 0.1 cm. Hip circumference will be measured at the widest part of the buttocks at the intertrochanteric level to the nearest 0.1 cm. All anthropometric measurements will be done by trained personnel.

##### Biochemical profile

Screening visit will include following measurements: total cholesterol, fasting glucose, liver profile (AST/GOT, ALT/GPT), kidney profile (creatinine, CKD-EPI e-GFR) and thyrotropin (TSH). Serum lipid profile: total, LDL, HDL cholesterol and triglycerides, liver profile (AST/GOT, ALT/GPT), kidney profile (creatinine, CKD-EPI e-GFR), fasting glucose, fool blood exam (FBE), leukocyte formula, electrolytes, cardiac/muscular markers (CK/myoglobin), CRP, and Lp(a) will be measured at baseline, 6 weeks, and on completion of the study (12 weeks from randomization). All items that will be measured at every visit are described in Table 2.

##### Clinical examinations

Seated blood pressure will be taken, two times with at least a 10-min rest between measurements using an Accoson mercury sphygmomanometer (M3 Intellisense Omron, Corman, Milano, Italy).

##### Electrocardiography

ECG will be recorded to verify the absence of using P8000 power by ESAOTE s.p.a, Firenze, Italy. The results of the ECG exam will be reported in the case report form (CRF) by the cardiologist.

##### Physical activity

Physical activity will be evaluated by using the International Physical Activity Questionnaire (IPAQ-SF) short form [21]. IPAQ-SF comprises a set of questionnaires that consider a time of person that spend being physically active in the last 7 days, for at least 10 min at a time. There are three kinds of physical activity: vigorous, moderate, and walking. Vigorous activities refer to hard physical effort that makes a person breathe much harder than usual. Moderate activities refer to moderate physical effort that makes a person breathe somewhat harder than usual. Walking includes any activity that one person has done for recreation, sport, exercise, or pleasure.

##### Other

Sociodemographic data will be evaluated using a tailored questionnaire, specifically designed for the study.

### Safety

At present, no adverse reactions related to the intake of this new dietary supplement are reported in the literature. However, in this study, all adverse events reported by the subjects or detected by the physician will be reported in the CRF, and all serious adverse events will be reported to the Ethics Review Committee.

### Retention

During the study, the participants will be encouraged by the physician to complete the follow-up. However, in case they still cannot complete the study, the motive for their withdrawal will be registered.

### Compliance calculation

Subjects will be asked to return the remaining capsules. The compliance will be evaluated by using the formula given below:
$$ \mathrm{Compliance}\ \left(\%\right)=\frac{\mathrm{Number}\ \mathrm{of}\ \mathrm{capsules}\ \mathrm{taken}}{\mathrm{Number}\ \mathrm{of}\ \mathrm{capsules}\ \mathrm{that}\ \mathrm{should}\ \mathrm{have}\ \mathrm{been}\ \mathrm{taken}}\times 100 $$

Compliance during the randomized period should be between 80 and 120%. Patients who will not be compliant with their treatment should again be carefully interviewed and reminded about the purpose and the conduct of the trial.

### Statistical analysis

Demographic, clinical characteristics and outcomes data will be summarized with counts and percentages for categorical variables, means (standard deviations) for normally distributed continuous variables, and medians (with interquartile ranges) for other continuous variables. Kolmogorov-Smirnov test will be used to check the normality of the related variables. Repeated measures analysis of variance (ANOVA) will be used to test whether treatment (between-subjects factor) differentially affect the mean values of cholesterol levels (within-subjects factor) over time. The same analysis will be also repeated for the inflammatory biomarkers that will be used as within-subjects’ factors. Mauchly’s test will be used to assess the assumption of sphericity, and Greenhouse-Geisser correction will be adopted for violations of this assumption. A significant level of 0.05 will be used throughout the study. Statistical analyses will be performed with IBM SPSS statistical software ver. 25.0 (IBM Corp., Armonk, NY, USA).

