### Sample size and statistical considerations

In the present study, 125 subjects will be recruited, randomized according to a 1:1 ratio in the intervention and the control arm. To find a significant difference in cholesterol levels between the two treatments (BruMeChol™ vs. placebo) at the end of the 2nd follow-up, assuming a medium effect size of the proposed treatment (*d* = 0.5), we should study at least 118 subjects (at least 59 for treatment arm) with a power of 0.85 and a type I error probability of 0.05. By providing a dropout rate of 5%, a total of 125 participants must be recruited.

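### The primary outcome and the sample size concern week 12, but the planned test is a repeated-measures ANOVA over all visits with no week-12 contrast named

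*Protocol article*

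**What the plan says.** All references are to the protocol article.

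- **Primary outcome:** the section reads "The primary outcome is the change in serum total cholesterol levels after 12 weeks", and it compares this change between the two arms.
- **Sample size and statistical considerations:** the aim is given as "To find a significant difference in cholesterol levels between the two treatments". The visit in question is set by the phrase "at the end of the 2nd follow-up". The effect is described by "assuming a medium effect size of the proposed treatment", and d is put at 0.5. Power is 0.85 and the type I error is 0.05. This gives 118 subjects (59 per arm), or 125 after 5% dropout. Sidedness is not stated.
- **Study period:** the visits are "baseline-randomization (visit 1), 6 weeks from baseline (1st follow-up, visit 2), and 12 weeks from baseline (2nd follow-up, visit 3"), so the second follow-up is week 12.
- **Statistical analysis:** "Repeated measures analysis of variance (ANOVA) will be used to test whether treatment (between-subjects factor) differentially affect the mean values of cholesterol levels" over time. The same section adds that "Mauchly’s test will be used to assess the assumption of sphericity", with a Greenhouse-Geisser correction if sphericity fails. It does not say which ANOVA term answers the primary question, and it names neither a week-12 contrast nor a baseline covariate.

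The article gives no standard deviation, no difference in mg/dL, no correlation between visits and no expected effect at week 6.

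**The concern.** The outcome and the sample size point to one quantity, the between-arm difference at week 12. The named analysis points to another. Sphericity is an issue only with three or more repeated levels, so the ANOVA must include baseline, week 6 and week 12. A test of whether treatment acts differently over those visits is the treatment-by-time interaction, with 2 degrees of freedom.

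That test treats baseline as a response and gives week 6 equal standing with week 12. It asks whether the between-arm difference varies at all across the visits. A significant F therefore need not mean a week-12 effect, and the F statistic carries no week-12 estimate or confidence interval. If the between-subjects main effect were read instead, it would average in baseline, where no treatment effect is possible.

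Two things are at stake: which result carries the primary claim, and whether 118 subjects give the intended power for the test that will be run.

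**Working it through.** **Inputs from the article:** n = 59 per arm, d = 0.5 at week 12, alpha 0.05, target power 0.85, 5% dropout, three visits.

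**Assumed:** the correlation ρ between visits (range shown), its structure, and the week-6 effect. All effects are in SD units.

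**1. The plan's own figure.** For a two-sample t-test at one time point, the noncentrality is d√(n/2) = 0.5 × √29.5 = 2.716 on 116 df.

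- One-sided 0.05: 59 per arm needed, 118 in total; power at 59 per arm 0.854. Dropout: 118/0.95 = 124.2, so 125. Both stated figures reproduce.
- Two-sided 0.05: 73 per arm needed, 146 in total (154 with dropout); power at 59 per arm 0.768. The stated figures do not reproduce.

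So 118 belongs to a one-sided comparison at a single visit, while the planned F test is non-directional and spans three visits.

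**2. Power at 59 per arm under compound symmetry.**

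- Interaction: λ = (n/2) Σ(δ − mean δ)² / (1 − ρ), on 2 and 232 df.
  - Effect building up, δ = (0, 0.25, 0.5): the sum is 0.125.
  - Effect full by week 6, δ = (0, 0.5, 0.5): the sum is 1/6.
- ANCOVA at week 12: λ = (n/2) d² / (1 − ρ²), on 1 and 115 df.

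For example, at ρ = 0.5:

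- interaction, building up: 29.5 × 0.125/0.5 = 7.375
- interaction, full by week 6: 29.5 × (1/6)/0.5 = 9.833
- ANCOVA: 29.5 × 0.25/0.75 = 9.833

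The last two have the same noncentrality, so the power gap between them (0.803 v 0.875) comes essentially from the second numerator degree of freedom.

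| ρ (assumed) | Interaction, building up | Interaction, full by week 6 | ANCOVA, week 12 |
|---|---|---|---|
| 0.3 | 0.520 | 0.651 | 0.806 |
| 0.5 | 0.674 | 0.803 | 0.875 |
| 0.7 | 0.887 | 0.959 | 0.965 |
| 0.8 | 0.976 | 0.996 | 0.994 |

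Total N for 85% power at ρ = 0.5 is 110 for ANCOVA and 178 (building up) or 134 (full by week 6) for the interaction.

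**3. Decaying correlation.** Here baseline and week 12 correlate at ρ and adjacent visits at √ρ. Interaction power with Greenhouse-Geisser was simulated (10,000 runs).

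| ρ (assumed) | Interaction, building up | Interaction, full by week 6 | ANCOVA, week 12 |
|---|---|---|---|
| 0.5 | 0.739 | 0.892 | 0.875 |
| 0.7 | 0.927 | 0.990 | 0.965 |

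**4. Specificity for week 12.** Take an effect at week 6 only, δ = (0, 0.5, 0). The sum of squares is 0.25 − 3 × (1/6)² = 1/6, the same as for an effect that is full by week 6 and lasts. Under compound symmetry the interaction test therefore cannot tell the two patterns apart. With no week-12 difference it rejects in 65% of trials at ρ = 0.3, 80% at ρ = 0.5 and 96% at ρ = 0.7.

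**5. If the between-subjects main effect is read instead.** λ = (n/2) × 3 × (mean δ)² / (1 + 2ρ). Over ρ = 0.3 to 0.8, power falls from 0.454 to 0.304 (building up) and from 0.691 to 0.488 (full by week 6).

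**The case against.** **The power loss depends on assumptions.** This stands. A reader might infer that the ANOVA always loses power against ANCOVA, but the article gives no correlation or week-6 effect, and the comparison slightly reverses in some cases. ANCOVA is also a benchmark from outside the protocol. Against the unadjusted two-sided comparison at week 12 (0.768), the interaction at ρ = 0.5 under compound symmetry lies on both sides (0.674 to 0.803). Part of the shortfall from 85% thus comes from the one-sided sizing and not from the ANOVA.

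**The outcome and the sample size do not conflict.** This stands. A reader might infer three different targets, because one section speaks of change and another of levels. Under randomisation the expected baselines are equal, so both have the same expected difference at week 12. There are two targets: week 12, and the test over time.

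**A condensed article may leave contrasts and intervals to a fuller document.** This stands in part. A reader might infer that the week-12 comparison will never be tested, and the article does not exclude visit-specific contrasts. But it does fix a method, and that method's own test does not answer the stated primary outcome. The point is that mismatch, not missing detail.

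**An effect at week 6 only is contrived.** Treatment runs for all 12 weeks, and nothing in the article predicts an effect that vanishes. The test also keeps its nominal error rate when there is no effect at any visit (0.048 to 0.052 in simulation). The scenario shows what a significant F fails to establish; it is not a forecast.

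**Week 6 has a place in the secondary analyses.** This stands: the secondary outcomes are defined at both 6 and 12 weeks.

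**Calling cholesterol the within-subjects factor is a slip.** This stands. The repeated factor is clearly visit, and nothing computed would change.

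**Conclusion.** The concern holds as a misalignment. The primary outcome and the sample size both target the between-arm difference at week 12, whereas the planned test is an omnibus test over three visits that can reject without any week-12 difference. The sample size was not derived for that test.

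This mismatch rests on the article's text and on no assumed value. The size of the power loss does rest on assumptions:

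- **Marked** at low to moderate correlation: about 7 points (0.875 − 0.803) to 29 points (0.806 − 0.520) for ρ of 0.3 to 0.5 under compound symmetry.
- **Still visible** at ρ = 0.7 when the effect builds up (0.887 v 0.965).
- **Negligible or slightly reversed** when the effect is full by week 6 and correlation is high (0.996 v 0.994 at ρ = 0.8) or decaying (0.892 v 0.875 at ρ = 0.5).

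A claim that the ANOVA is generally less powerful would go beyond what the article supports.

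**What to change.** Make the primary analysis a two-sided ANCOVA of week-12 total cholesterol on treatment and baseline total cholesterol, reporting the adjusted mean difference with its 95% CI. An alternative is a mixed model for weeks 6 and 12 with treatment-by-visit and baseline-by-visit terms and a pre-specified week-12 contrast. The baseline-by-visit term is needed for it to match the ANCOVA when data are complete.

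Keep the repeated-measures ANOVA as supportive. As a wording correction only, name visit as its within-subjects factor.

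State the sidedness behind the 118. With a two-sided 0.05 test at 59 per arm, ANCOVA reaches 0.806 at ρ = 0.3 and 0.875 at ρ = 0.5, so whether the 85% target is met depends on the correlation.

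The cost is a change of wording before unblinding. Total cholesterol is already measured at baseline, week 6 and week 12, and the planned software fits these models. No extra visits, samples or subjects are needed for the change of analysis.
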